## Abstract

**Background:**

The aim of this prospective study is to investigate the diagnostic performance of integrated positron emission tomography (PET) /dual-energy computed tomography (DECT) imaging in determining the thoracic nodal status of patients with small-cell lung cancer (SCLC) or non-small-cell lung cancer (NSCLC) and the resulting impact on target volume delineation for radiation therapy planning.

**Methods:**

This is a single-center prospective study including approximately 50 patients with suspected or confirmed SCLC or NSCLC, referred for a PET study. All patients will be examined on a clinical PET/DECT system, where a dual-energy detector was recently installed. The patient will be placed in the system 70 min after the administration of 5 MBq/kg of ^18^F-fluorodeoxyglucose (^18^F-FDG). Then, DECT will be acquired after the injection of 100 mL of iodine contrast medium. A PET scan will be acquired from the top of the skull through the inguinal region. Data analysis will be performed on the PET, CT, and iodine map datasets. Information regarding tumor detection, adenopathies, and radiation therapy planning will be assessed based on all three sets of images by two experienced radiologists.

**Conclusion:**

The results will add insights into the advantages of using PET/DECT for lung cancer staging and for image-guided radiation therapy.

**Trial registration:**

ClinicalTrials.gov, NCT03146117. Registered on 9 May 2017.

## Key points

PET/CT is the established standard for planning lung cancer radiation therapyPET/DECT may improve accuracy for lung tumor detection and nodal stagingPET/DECT may improve accuracy for radiation therapy planning

## Background

^18^F-fluorodeoxyglucose (^18^F-FDG) positron emission tomography (PET) plays an important role in the staging of small-cell lung cancer (SCLC) and non-small-cell lung cancer (NSCLC). Multiple studies have demonstrated the utility of PET for improving staging accuracy, with respect to the mediastinum and distant metastatic involvement compared to computed tomography (CT) alone [1–5]. Additional improvements in staging accuracy are encountered when functional PET imaging is combined with CT in integrated and dedicated PET/CT systems [6, 7]. Furthermore, PET/CT should be used for image-guided radiation therapy (IGRT) planning because it images tumor extent with greater accuracy than CT alone increasing normal tissue sparing from futile irradiation, especially in case of atelectasis, and provides a better assessment of involved nodes [8, 9].

Despite the higher accuracy of PET/CT, the limitations of PET should be recounted. The rate of false-negative lymph node station assessment in patients with NSCLC candidates to radiation therapy is reported to be in the range of 5–10% [10]. Small lesions (< 1 cm) are difficult to identify and in the setting of elevated blood glucose the consequent decrease in tumor ^18^F-FDG-PET uptake may cause a false-negative result [11]. False-negative scans can also occur soon after chemotherapy [9]. Regarding IGRT planning, the margins of PET-detected lesions can appear blurred due to respiration. Moreover, a large degree of uncertainty exists regarding the most appropriate standard uptake value (SUV) threshold cut-off value that would ideally define a PET target volume in NSCLC treatment planning [12].

Dual-energy CT (DECT) is a relatively new imaging technique, whose basic principle is the application of two distinct energy settings with the transition from CT density-based imaging to material-specific or spectral imaging [13]. The possibility to generate iodine map images, which enable an accurate quantification of iodine uptake within a lesion could represent a reliable quantitative biomarker for tumor detection and lymph node characterization [14].

In the literature, the advantages of combined PET/DECT imaging in determining the nodal status of patients with SCLC or NSCLC as well as in guiding radiation therapy planning have not been investigated. Thus, this study has been designed to assess the role of the first integrated PET/DECT system for staging and IGRT planning in lung cancer [15, 16].

## Methods

### Study design and patient population

This is a prospective, single-center study designed to evaluate a novel PET/DECT system in patients with suspected or confirmed SCLC or NSCLC who are referred to undergo a clinically indicated PET/CT for staging. We plan to recruit approximately 50 individuals either male or female, in the age range of 18–90 years, with suspected or confirmed SCLC or NSCLC referred to undergo a clinically indicated ^18^F-FDG-PET/CT examination (Fig. 1).

**Fig. 1 Fig1:**
[figure not shown]
Study design *flowchart*. *SCLC* Samall-cell lung cancer, *NSCLC* Non-small-cell lung cancer, *PET/DECT* Positron emission tomography/dual-energy computed tomography, *RT* Radiation therapy

Clinical staging will be performed using the 8^th^ edition TNM classification system by the American Joint Committee on Cancer [17] based on CT, PET/CT, and brain magnetic resonance, as clinically indicated. Pathologic staging may incorporate percutaneous biopsy, endobronchial ultrasound, and surgery determined by accepted clinical guidelines. Institutional Review Board review and approval will be obtained before commencing enrollment. The inclusion and exclusion criteria are summarized in Table 1.

**Table 1 Tab1:** Patient eligibility criteria

	Inclusion criteria		Exclusion criteria
1	Subject must have a suspected SCLC or NSCLC	1	Subject is a pregnant or nursing female
2	Subject must be aged 18–90 years	2	Subject is in acute unstable condition
3	Subject must have been referred for a clinically indicated PET/CT	3	Subject is unwilling to comply with the requirements of the protocol
4	Subject must provide written informed consent before any study-related procedures being performed	4	By testing (serum or urine βHCG) within 24 h before contrast, agent administration, or by surgical sterilization, or post-menopausal, with minimum one-year history without menses
5	Subject must be willing to comply with all clinical study procedures	5	Subject has an allergy against iodinated contrast agents and cannot be premedicated
		6	Subject has impaired renal function (eGFR < 30 mL/min × 1.73 m^2^)
		7	Subject has an acute psychiatric disorder or is cognitively impaired
		8	Subject is using or is dependent on substances of abuse

*SCLC* small-cell lung cancer, *NSCLC* non-small-cell lung cancer, *PET/CT* positron emission tomography / computed tomography, *βHCG* β-human chorionic gonadotropin, *eGFR* estimated glomerular filtration rate

### Study objectives

The overall goal of this project is to investigate the diagnostic performance of integrated PET/DECT imaging in determining the thoracic nodal status of patients with SCLC or NSCLC and its impact on target volume delineation for IGRT planning.

### Imaging protocol

All patients will be examined on a clinical PET/CT system (Biograph mCT, Siemens Healthineers, Forchheim, Germany), where a dual-energy detector (TwinBeam Dual Energy, Siemens Healthineers, Forccheim, Germany) has been installed (Fig. 2). Patients will be placed in the supine position with both arms raised above their head. Our standard clinical PET/DECT protocol includes a non-breath-hold contrast-enhanced DECT scan with the arms down for attenuation correction, acquired from the top of the skull through the inguinal region, followed by a shallow breath DECT scan of the chest, acquired from the pulmonary apex through the diaphragm, with the arms up. For contrast injection, we will use an automatic double-head power injector to administer a total of 100 mL of non-ionic iodinated contrast material at a flow rate of 3.0 mL/s, followed by a 20-mL saline flush.

**Fig. 2 Fig2:**
[figure not shown]
**a** Integrated PET/DECT system. **b** Particular of the TwinBeam dual-energy system

The patient will be placed in the system 70 min after the administration of 5 MBq/kg of ^18^F-FDG. The patient fasting glucose level will be measured before the injection. A PET scan will be acquired from the top of the skull through the inguinal region. A three-dimensional (3D) emission scan of the same areas will be acquired.

Axial CT datasets will be reconstructed using a 3-mm section thickness and increment. Low-energy 120 kVpSn (tin filtration) and high-energy 120 kVpAu (gold filtration) datasets [18] will be loaded into a dedicated dual-energy post-processing workstation (Siemens Multi-Modality Workplace MMWP, Siemens Healthineers, Forccheim, Germany) and a mixed standard 120-kV dataset and iodine-map dataset will be generated by using an application available on the workstation (Dual Energy Syngo, Siemens Healthineers, Forccheim, Germany). Twin-beam datasets were used to generate linearly blended and noise-optimized virtual monoenergetic images at 50 keV using iterative reconstruction strength 3 (Safire, Siemens Healthineers, Forccheim, Germany). To generate iodine map images, standard soft-tissue and fat attenuation values in default settings will be used (soft tissue and fat attenuation of 60/55 HU and − 110/− 87 HU at low/high kVp, respectively); beam-hardening correction, organ contour enhancement, and resolution enhancement will be also applied (Fig. 3).

**Fig. 3 Fig3:**
[figure not shown]
PET and DECT images comparison in a patient with lung cancer and metastatic right hilar adenopathy. **a** Fused PET/CT dataset showing metabolic uptake of the right hilar adenopathy and lung mass (*arrow*). **b** Dual-energy iodine map dataset showing iodine uptake in the same region (*arrow*)

### Data analysis

#### Tumor detection

Before analysis, images from each patient will be separated into three groups (PET, CT, iodine-map) corresponding to three different datasets. Images will be all reviewed on a picture archiving and communication system workstation. Two radiologists with > 5 years of experience will independently analyze the number of pulmonary lesion(s), mediastinal and hilar adenopathies, and distant metastases in the three datasets in separate reading sessions. Lymph nodes will be considered to be involved if they demonstrate a SUV > 3.0 on PET, a short axis ≥ 10 mm in diameter on CT, or a iodine reduction on the iodine-map (mean iodine concentration < 2.5 mgI/mL). For each lesion, the CT diameter, CT attenuation, iodine concentration, and SUV will be measured using a region of interest drawn by the radiologist. Radiologists will be blinded to patient identity, lesion number, and the results of other imaging studies. To avoid recall bias, the time interval between each of the reading sessions will be at least two weeks. After this blind evaluation, the study coordinator will review all images and match the imaging findings with the lesions marked by each reader in each dataset. The reference standard will be the complete evaluation of the PET/CT performed separately from the individual components above. Discrepancies between radiologists will be handled in consensus.

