### Statistical analysis

All analysis will be performed using Statistical Analysis System (SAS 9.4, Cary, NC, USA). This is a pilot study with a convenience sample of 50 participants for Aim 1 (approximately 5–10 lymph nodes per patient) and the first 20 participants who undergo radiation therapy treatment for Aim 2. The analysis will include node-based analysis and patient-based analysis.

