#### Aim 1: node-based analysis

Descriptive statistics will summarize the location and the number of positive cases for each lymph node using CT (where the test positive is defined as a lymph node short axis diameter > 1 cm), PET (where the test positive is defined as that SUV > 3.0), and DECT (where the test positive is defined as that the iodine is < 2.5 mgI/mL). To address clustering, we will perform a multilevel model test. The diagnostic power will be summarized by the area under the curve at receiver operating characteristic analysis (AUC), comparing CT and PET, CT and DECT, as well as PET and DECT. Multilevel models will be used to estimate the probability of a positive, which will be used to estimate the empirical AUC. The following additional analysis will be done to further understand the performance of CT, PET, and DECT. First, the Cohen’s κ statistics will be used to assess the concordance between CT and PET, DECT and PET, and DECT and CT. Second, for patients with known disease status, the AUC will be evaluated comparing CT and PET, and DECT and PET, using the complete PET/CT examination and the pathological specimens, if available, as a reference standard for lesion detection and characterization.

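### The reference standard for nodal accuracy is built from PET and CT, two of the three tests being judged, so the PET-versus-DECT AUC comparison is biased in favour of PET

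*Protocol article*

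**What the plan says.** Under Data analysis, Tumor detection, "images from each patient will be separated into three groups (PET, CT, iodine-map) corresponding to three different datasets", and two radiologists read each dataset in separate sessions. A node counts as involved on "a SUV > 3.0 on PET, a short axis ≥ 10 mm in diameter on CT, or a iodine reduction on the iodine-map". The same section then fixes the truth: "The reference standard will be the complete evaluation of the PET/CT performed separately from the individual components above". Pathology is not mentioned there.

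Under Statistical analysis, Aim 1, diagnostic power is summarised by the AUC, "comparing CT and PET, CT and DECT, as well as PET and DECT"; no reference standard is attached to that sentence. A later, additional AUC analysis is limited to patients with known disease status and compares CT with PET and DECT with PET, "using the complete PET/CT examination and the pathological specimens, if available, as a reference standard for lesion detection and characterization".

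How often tissue will exist is not stated. The Study design section says: "Pathologic staging may incorporate percutaneous biopsy, endobronchial ultrasound, and surgery determined by accepted clinical guidelines". The Background acknowledges that PET nodal assessment errs: the false-negative rate for nodal stations "is reported to be in the range of 5–10" per cent. The Discussion hopes that the work may improve the accuracy of PET/CT for thoracic adenopathy.

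**The concern.** An accuracy measure means what it says only if the reference is independent of the test. Here the reference is an overall reading of the same PET and CT images that supply two of the three index tests. Reading them separately removes the influence of one reading on the other. It does not remove the shared images, so an error in the PET image tends to appear in both the PET call and the reference, where it counts as agreement. The iodine map is not named as part of the reference and gets no such credit.

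This is incorporation bias, and it works against the modality the study is meant to evaluate. The nodes where iodine data could add something are those where PET/CT is wrong. Without tissue, each of those nodes that DECT classifies correctly is recorded as a DECT error. More patients would not help, since the bias does not depend on sample size. A pilot analysed this way could rank DECT below PET and discourage further work when the true order is the reverse.

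**Working it through.** The protocol gives no expected accuracy, prevalence or power (it is a convenience sample), so there is no figure of its own to reproduce. The check asks what AUC the plan would report for tests of known accuracy.

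**Inputs.** From the protocol: three binary tests, and a PET/CT reference with pathology at some nodes. Assumed: true sensitivity/specificity of PET 0.80/0.90, CT 0.60/0.80, DECT 0.90/0.95; prevalence π = 0.3; tests independent given true node status; pathology in a random share v of nodes. The protocol does not say how PET and CT are combined, so three rules are shown: the reference follows PET; either is positive; both are positive.

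**Formulas.** The AUC of a binary test is (Se + Sp)/2. The true values are PET (0.80 + 0.90)/2 = 0.850, CT 0.700, DECT 0.925. Let a and b be the probabilities that the imaging reference is positive in involved and uninvolved nodes. With pathology in a share v, a′ = v + (1 − v)a and b′ = (1 − v)b. For DECT:

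- apparent Se = [πa′·Se + (1 − π)b′(1 − Sp)] / [πa′ + (1 − π)b′]
- apparent Sp = [π(1 − a′)(1 − Se) + (1 − π)(1 − b′)Sp] / [π(1 − a′) + (1 − π)(1 − b′)]

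**No pathology, reference follows PET** (a = 0.80, b = 0.10). Reference-positive share: 0.24 + 0.07 = 0.31. DECT Se = (0.24×0.90 + 0.07×0.05)/0.31 = 0.2195/0.31 = 0.708. DECT Sp = (0.06×0.10 + 0.63×0.95)/0.69 = 0.6045/0.69 = 0.876. AUC = 0.792. PET agrees with itself, so its AUC is 1.000.

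**No pathology, either positive** (a = 1 − 0.2×0.4 = 0.92, b = 1 − 0.9×0.8 = 0.28). Reference-positive share: 0.276 + 0.196 = 0.472. DECT Se = 0.2582/0.472 = 0.547, Sp = 0.4812/0.528 = 0.911, AUC 0.729. PET Se = 0.31/0.472 = 0.657, Sp = 1, AUC 0.828.

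**No pathology, both positive** (a = 0.48, b = 0.02). Reference-positive share: 0.144 + 0.014 = 0.158. DECT Se = 0.1303/0.158 = 0.825, Sp = 0.6673/0.842 = 0.793, AUC 0.809. PET Se = 1, Sp = 0.69/0.842 = 0.819, AUC 0.910.

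**Half of nodes with pathology.** Example, reference follows PET: a′ = 0.90, b′ = 0.05. DECT Se = 0.24475/0.305 = 0.802, Sp = 0.63475/0.695 = 0.913, AUC 0.858. PET Se = (0.12 + 0.155)/0.305 = 0.902, Sp = (0.315 + 0.345)/0.695 = 0.950, AUC 0.926.

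| Reference at nodes without tissue | PET v DECT, no pathology | PET v DECT, pathology in half |
|---|---|---|
| Follows PET | 1.000 v 0.792 | 0.926 v 0.858 |
| Either positive | 0.828 v 0.729 | 0.828 v 0.809 |
| Both positive | 0.910 v 0.809 | 0.863 v 0.869 |
| Truth (pathology in all) | 0.850 v 0.925 | 0.850 v 0.925 |

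At prevalence 0.5 without pathology the same three rules give 1.000 v 0.801, 0.875 v 0.783 and 0.867 v 0.761.

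**No true difference.** If DECT is given PET's accuracy (both 0.850, prevalence 0.3, no pathology), the plan would report 1.000 v 0.741, 0.828 v 0.689 and 0.910 v 0.754: a PET advantage where none exists.

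**From the protocol's own error rate.** It expects 50 × 5 = 250 to 50 × 10 = 500 nodes. Suppose 70% are PET/CT-negative (assumed) and read the 5–10% as the share of those that are truly involved (one possible reading). Then 250 × 0.70 × 0.05 ≈ 9 to 500 × 0.70 × 0.10 = 35 correct positive calls by a perfect DECT would count as false positives if no tissue were taken, and its apparent specificity could not exceed 90–95%.

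**The case against.** The best defence has four parts.

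*Pathology is in the plan.* The Aim 1 section adds tissue where available, so it supplements the Tumor detection section rather than flatly contradicting it, and the unlabelled first AUC may simply inherit the standard given there. That is fair, but it does not help: tissue is optional and its share unknown, and inheriting the earlier standard means PET/CT alone, the least favourable case for DECT.

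*The strong readings fail.* A reader might infer that DECT can never be shown to beat PET. The protocol does not support this, because tissue-verified nodes can be scored correctly and the combination rule is open. In the table DECT leads narrowly (0.869 v 0.863) with half the nodes verified and a both-positive rule. With PET 0.80/0.98, CT 0.60/0.98, DECT 0.99/0.99, prevalence 0.3, an either-positive rule and no tissue, DECT still leads 0.928 v 0.918, although the true lead of 0.990 − 0.890 = 0.100 has shrunk to 0.010. A reader might also infer that PET and CT both score too high in absolute terms. They need not: CT falls from 0.700 to 0.637 when the reference follows PET, and PET from 0.850 to 0.828 under the either-positive rule. The reliable statement is relative: PET gains on DECT.

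*The numbers are assumed.* Independence given truth is doubtful, since the mixed CT images and the iodine map come from the same twin-beam acquisition. The sizes are illustrations. The direction was the same in every setting run without full pathology.

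*It is a pilot with no formal superiority hypothesis.* True, and the protocol's language is exploratory. Aim 1 nevertheless plans AUC comparisons, and these would be read as accuracy.

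**Conclusion.** The point stands in relative form. The plan as written biases the PET-versus-DECT AUC comparison towards PET, because PET and CT belong to the reference and the iodine map is not named as part of it. With a true DECT lead of 0.075, PET appears ahead by 0.208, 0.099 and 0.101 under the three rules without pathology. With pathology in a random half of nodes it is ahead by 0.068 and 0.019 under the first two, and DECT is ahead by 0.006 under the third. So a real advantage is shrunk and often reversed, but not always hidden.

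These sizes rest on assumed accuracies, prevalence, independence and random verification. The direction rests on the structure of the reference. The kappa statistics between modalities and the Aim 2 comparison of gross tumor volumes do not use this reference and are unaffected.

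**What to change.** State one standard, in the same words, in the Tumor detection and Aim 1 sections, and attach it to every AUC comparison, including the first.

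- Use pathology already obtained for care as the reference for AUC, sensitivity and specificity.
- For nodes without tissue, report results against the complete PET/CT only as agreement (kappa, positive and negative percent agreement), and do not call it accuracy.
- Report how many nodes were verified and how they came to be sampled.

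This changes wording and analysis only; no procedure is added. The price is precision and selection. If a share v of the 250–500 nodes has tissue, the accuracy analysis keeps 250v to 500v of them. At one half that is 125–250 nodes, with intervals wider by about 1/√0.5 = 1.41, ignoring clustering. Sampling follows clinical guidelines and clinical staging uses CT and PET/CT, so the verified nodes will not be a random subset. Partial verification bias then remains and must be stated as a limitation.

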#### CT simulation for radiation therapy planning

Patients who will receive radiation therapy for locally advanced lung cancer will be simulated with immobilization to assure reproducibility of the setup. Each patient will be positioned in an immobilization device in the treatment position on a flat Table. A volumetric planning CT will be performed with no more than 3-mm thickness from the level of the cricoid cartilage through the entire liver volume. Four-dimensional radiation planning is required and can include design of the planning target volume (PTV) to account for primary and nodal tumor motion during free breathing or the more limited excursion during deep inspiration breath-hold with a real-time position management system (RPM, Varian Medical System, Palo Alto, CA, USA).

#### Virtual simulation and 3D treatment planning

The fused images will be transferred to a dedicated workstation. The gross tumor volume (GTV) will be defined by the planning physician as all known gross disease (gross tumor volume, pulmonary [GTV-P]) and involved mediastinal and hilar nodes (GTV-N) as demonstrated on the treatment planning scans. Two GTVs contours will be outlined by the same radiotherapist for each patient. The first volume will be defined from the anatomic data provided by PET/CT and the second volume will be defined from the anatomic data provided by PET/DECT. The GTV-N will include only those lymph nodes considered to be involved. As already stated above, lymph nodes will be considered to be involved in PET/CT and in PET/DECT when they demonstrate an increased ^18^F-FDG uptake (SUV > 3.0) and/or an iodine reduction on the iodine-map (< 2.5 mgI/mL). In addition, any nodes pathologically confirmed to be involved will be included. Non-involved elective nodal regions will be not intentionally targeted.

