#### Aim 2: patient-based analysis

We will evaluate the impact of DECT and FDG-PET image fusion on treatment planning in 20 patients out of the 50 recruited who will receive radiation therapy at our institution. Descriptive statistics will be used to summarize GTV measure. A Wilcoxon Signed-Rank test will be used to explore the statistical difference of the above measurements between PET/CT and PET/DECT.

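### As written, the PET/CT contour comes first and the PET/DECT contour second for every patient, with no stated interval or masking, so the Aim 2 difference could mix imaging, second-look and anchoring effects

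*Protocol article*

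**What the plan says.** The protocol article, under Virtual simulation and 3D treatment planning, states: "Two GTVs contours will be outlined by the same radiotherapist for each patient". PET/CT is the source of one volume and PET/DECT of the other, in this order: "The first volume will be defined from the anatomic data provided by PET/CT and the second volume will be defined from the anatomic data". The same assignment applies to every patient. The section gives no interval between the two contours, does not say whether the first is hidden while the second is drawn, and mentions no random or balanced order.

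The Tumor detection section treats the radiologists' readings differently. It uses separate sessions and states: "To avoid recall bias, the time interval between each of the reading sessions will be at least two weeks". It adds: "Radiologists will be blinded to patient identity, lesion number, and the results of other imaging studies".

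Under Statistical analysis, Aim 2 takes "the first 20 participants who undergo radiation therapy treatment for Aim 2". Under Aim 2: patient-based analysis, "A Wilcoxon Signed-Rank test will be used to explore the statistical difference of the above measurements between PET/CT and PET/DECT". No adjustment for order is mentioned.

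**The concern.** A paired design removes differences between patients, and using one contourer per patient removes differences between observers. Neither removes what happens within the contourer between the first and second attempt.

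Two mechanisms matter. On a second look at the same patient, the contourer may systematically enlarge or tighten the volume whatever images are shown. And if the first contour is remembered or visible, the second may be pulled towards it. If PET/CT always comes first, the first mechanism is credited to DECT and the second hides part of what DECT does.

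Impact on target volume delineation is one of the two parts of the overall goal under Study objectives, and the Discussion speculates that less lung might be irradiated. A second-look tightening would look like support for that idea, and anchoring would look like evidence against it. A fixed order cannot be repaired in the analysis, because no patient would have been contoured in the other order.

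**Working it through.** **Plan's own figure.** There is none to reproduce. Aim 2 is a convenience sample of 20 with no stated power, effect size, SD or significance level.

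**Inputs.** From the protocol article: n = 20, paired comparison, PET/CT first and PET/DECT second. Assumed here: two-sided 5% level, normally distributed paired relative differences, SD of 10%, 15% or 20%, and a second-look drift of 3%, 5% or 7%. The documents support none of the assumed values, nor the direction of any drift.

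**What the difference estimates.** Let δ be the imaging effect, s the second-look shift, and λ the fraction by which the second contour is pulled towards the first. Let D be the PET/DECT volume minus the PET/CT volume.

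- PET/CT first for everyone: E(D) = (1 − λ)(δ + s). One observed mean carries three unknowns.
- Order balanced 10/10, same λ in both orders: E(D) = ½(1 − λ)[(δ + s) + (δ − s)] = (1 − λ)δ. The shift s cancels; the shrinkage λ does not.

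Balancing therefore deals with a simple order shift. Anchoring needs the interval and the masking.

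**Size of the second-look problem (δ = 0, λ = 0).** I used a noncentral t approximation with noncentrality = drift ÷ SD × √20 and 19 degrees of freedom. For a 5% drift and 15% SD this is 0.05 ÷ 0.15 × 4.472 = 1.49, a rejection probability of 29%.

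| SD of paired difference | Drift 3% | Drift 5% | Drift 7% |
|---|---|---|---|
| 10% | 25% | 56% | 84% |
| 15% | 14% | 29% | 51% |
| 20% | 10% | 19% | 32% |

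Simulating the signed-rank test itself (n = 20, reject if the smaller rank sum is at most 52) gives about 54%, 28% and 18% for a 5% drift at SDs of 10%, 15% and 20%. With no drift it gives just under 5%. The approximation is adequate.

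**With the order balanced 10/10.** The same simulation with a 5% drift and no imaging effect gives about 3%, 4% and 4% at those SDs, and the mean difference is centred on zero.

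**Anchoring.** If the pull is proportional, every paired difference is multiplied by (1 − λ). The estimate shrinks by that factor, but the signed-rank test does not depend on scale. A true effect of 0.7 SD is rejected in about 82% of simulated studies with no pull, a 25% pull or a 50% pull. Power falls (to about 58% and 30%) only if the mean shrinks while the SD stays fixed. The secure statement is that anchoring biases the volume estimate.

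**The case against.** Several counter-arguments have force.

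- **The words first and second may only label the two volumes.** This is possible. Sequence is the natural reading and no other order is given, but it is not the only reading. If they are labels, full confounding of order with modality is not established; possible carry-over between two contours by the same person remains.
- **Silence on interval and masking is normal in a condensed article.** In part. The article does not say that the first contour is visible during the second. But it sets an interval and blinding for the readings, names recall bias as the reason, describes contouring in similar detail, and offers neither there.
- **One contourer per patient is sound.** Agreed, and the fix keeps it. A reader might infer one person for the whole study; the text says only the same one for each patient.
- **The contourer cannot be blinded to modality.** True. Only the earlier contour can be hidden.
- **PET/CT first may be deliberate.** The mixed 120-kV images and the iodine map come from the same twin-beam data (Imaging protocol), so PET/DECT is in essence PET/CT plus iodine information. Reversing the order lets remembered iodine findings affect some PET/CT contours. This stands, and it is why balancing alone is not enough.
- **Node inclusion follows numeric thresholds and pathology.** This leaves less room for drift in which nodes enter GTV-N. The concern falls mainly on GTV-P margins and node outlines.
- **Aim 2 is exploratory.** The Statistical analysis section calls the study a pilot, and no confirmatory claim rests on the test.

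**Conclusion.** The concern holds in a conditional form. On the natural reading, modality and contouring order coincide in all 20 patients. The paired difference could then contain a second-look effect and anchoring as well as the imaging effect, with unknown net direction.

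The size is illustrative only: about 19% to 56% nominally significant results with no imaging effect, for an assumed 5% drift and SDs of 20% down to 10%. Anchoring would shrink the estimated volume difference by whatever fraction the second contour is pulled.

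A reader might infer more: that a fixed order necessarily produces a non-zero difference, that anchoring must cost power, or that Aim 2 is invalid. The documents support none of these. Drift must be systematic to shift the result, proportional anchoring leaves the signed-rank test unchanged, and the test is stated to be exploratory. What is at risk is the interpretation of the pilot's effect estimate. The change should be made before contouring starts.

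**What to change.** 1. State whether first and second denote a time order.
2. Keep the same radiotherapist for both contours of a patient.
3. Hide the first contour while the second is drawn, and separate the two sessions by at least the two weeks already used for the radiologists' readings.
4. Balance the order by a randomised list, 10 patients each way, always together with step 3. Report the paired difference by order descriptively. A test between orders would be weak: at 5% drift and 15% SD, the groups differ by 2 × 5% = 10% with standard error 15% × √(1/10 + 1/10) = 6.7%, giving power of about 29%.
5. If PET/CT is kept first so that the baseline stays free of iodine information, apply step 3 all the same, and describe the result as the effect of adding DECT information on a second contouring, not of DECT alone.

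The cost is a short list and scheduling for 20 patients, with no extra scans or staff; the second study contour is drawn later. It would be tempting to say that these are research contours and cannot delay care, but the documents do not say which contour is used for treatment. The protocol should state this, so that the interval does not affect care.
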